## Abstract

**Purpose::**

Overall complication and leak rates in colorectal surgery showed only minor improvements over the last years and remain still high. While the introduction of the WHO Safer Surgery Checklist has shown a reduction of overall operative mortality and morbidity in general surgery, only minor attempts have been made to improve outcomes by standardizing perioperative processes in colorectal surgery. Nevertheless, a number of singular interventions have been found reducing postoperative complications in colorectal surgery. The aim of the present study is to combine nine of these measures to a catalogue called *colorectal bundle* (CB). This will help to standardize pre-, intra-, and post-operative processes and therefore eventually reduce complication rates after colorectal surgery.

**Methods::**

The study will be performed among nine contributing hospitals in the extended north-western part of Switzerland. In the 6-month lasting control period the patients will be treated according to the local standard of each contributing hospital. After a short implementation phase all patients will be treated according to the CB for another 6 months. Afterwards complication rates before and after the implementation of the CB will be compared.

**Discussion::**

The overall complication rate in colorectal surgery is still high. The fact that only little progress has been made in recent years underlines the relevance of the current project. It has been shown for other areas of surgery that standardization is an effective measure of reducing postoperative complication rates. We hypothesize that the combination of effective, individual components into the CB can reduce the complication rate.

**Trial registration::**

Registered in ClinicalTrials.gov on 11/03/2020; NCT04550156.

**Highlights:**

**Purpose:**

**Methods:**

**Discussion:**

## 1. Introduction

Complications after colorectal surgery are encountered in up to 40% of patients with anastomotic leakage being the most feared potentially fatal outcome [1,2,3]. Multiple patient factors such as immunosuppression, malnutrition or severe comorbidities as well as surgeon`s and institutional factors such as caseload are known to influence the risk of complications [4,5,6]. While reported overall complication and leak rates showed only minor or no improvements over time, they differ dramatically between institutions, depending on patient`s and surgeon`s selection [5,7]. Surgical Site Infection (SSI) is a key indicator for postoperative complications in colorectal surgery. In North Western Switzerland reported anastomotic leak rates after colorectal resection range from 1.5 to 22% on an institutional level reflecting different case selection as well as surgical practice in the contributing institutions [8].

Recent research showed, that standardization is one possible measure to reduce complication rates in surgery. The introduction of the perioperative WHO Safer Surgery Checklist, for example has shown a reduction of overall operative mortality and morbidity in general surgery for high- and low-income countries [9,10]. While this has led to a widespread implementation of the checklist in most developed countries including Switzerland, only few attempts have been made to improve outcomes by standardizing the peri- and intraoperative process in colorectal surgery so far [11]. J.K. Lovely et al showed, that the implementation of an enhanced recovery pathway including preoperative analgesia, limited intravenous fluids and opiates, and early feeding, led to a significant reduction of hospitalization time in minimal invasive colorectal surgery [12]. One of the most far-reaching changes by standardization in colorectal surgery has been achieved by the introduction of the Enhanced Recovery After Surgery (ERAS) guidelines by the Society for colorectal surgery. This program, which consists of various measures for whose effectiveness there is good evidence, has had a lasting impact on the perioperative management of patients undergoing colorectal surgery [13].

Nevertheless, a number of other interventions have been found to be useful in the reduction of postoperative complications in colorectal surgery involving the following items:

Risk stratification of patients undergoing colorectal anastomosis can lead to a more profound and joint decision making with patients and the surgical team at what risk a particular patient will be and which patients might benefit from temporary diversion [5].According to Centre for Disease Control (CDC) Guidelines for prevention of SSI patients should shower or bath (full body) with soap (antimicrobial or nonantimicrobial) or an antiseptic agent no longer than the night before surgery [14].The implementation of antibiotic decontamination and mechanical bowel preparation has led to a reduction of SSI in randomized trials and a reduction of anastomotic leakage in large retrospective cohort studies [15,16].As malnutrition has been identified as a key correctable risk factor in elective colorectal surgery a standardized nutritional screening should be performed among all surgical candidates. This allows for targeted nutritional support in patients with low BMI/protein levels or recent relevant loss of weight [17].Adherence to WHO guidelines for intravenous antibiotic prophylaxis including proper timing within 60 minutes prior to incision as well as repetition after prolonged surgery has shown to reduce SSI rates [18,19].Intraoperative anesthetic measures such as the optimization of perioperative glucose levels and securing euthermia of the patient has shown a positive effect on SSI rates [20,21,22].Preparing the operative field with hair removal using clippers instead of shaving has been successfully used to reduce superficial SSI [23].In a recent meta-analysis, the use of intraoperative wound protectors was associated with reduced SSI in lower gastrointestinal surgery [24]. In addition, changing gloves and instruments after the contaminated part of the procedure (opening the bowel) led to a reduction in SSI rates [25].The presence of an experienced colorectal surgeon in the operation room during the formation of the anastomosis was associated with reduced complications and ostomy formation in large retrospective cohort studies [26].

All these peri- and intraoperative measures can be combined to a *colorectal bundle* (CB) to improve overall quality of care and reduce complications in colorectal surgery. To the knowledge of the authors such a comprehensive bundle has not yet been introduced.

### 1.1 Objectives

The primary objective of this study is whether the introduction of the above-mentioned quality improvement measures in a CB can reduce complication rates measured based on a reduction of the Comprehensive Complication Index (CCI) compared to the current standard [27]. We hypothesize that the introduction of the CB will lead to an overall reduction of the CCI of at least 10 points in the contributing hospitals of the Swiss North Western Hospital Network.

Secondary objectives are to

– assess the impact of the CB protocol on SSI– assess the impact of the CB protocol on mortality– assess the impact of the CB protocol on hospital length of stay– assess the impact of the CB protocol on contribution margin measured as the difference between allocated costs and billed and paid income for a particular case– assess the impact of the CB protocol on anastomotic leak rates– identify risk factors for anastomotic leakage and higher CCI (>30) in colorectal resections– assess the impact of the inclusion of antibiotic decontamination (facultative) into the CB in a subgroup of hospitals on CCI

## 2. Methods: Participants, interventions, and outcomes

### 2.1 Study settings

The study will be conducted in a hospital network of nine contributing hospitals in the extended north west of Switzerland. To increase generalizability, the composition of the network reaches from reference centres like the University Hospital Basel and the St. Clara Spital to middle sized cantonal hospitals. It thus covers a large health care area with a drainage area of approximately 1.5 million persons. The contributing hospitals are Clarunis University Centre for Gastrointestinal and Liver Diseases Basel with the two sites University Hospital Basel and St. Claraspital, Cantonal Hospital Baselland Liestal, Cantonal Hospital Olten, Cantonal Hospital Lucerne, Spitalzentrum Biel, Cantonal Hospital Aarau, Limmattalspital Schlieren and Lindenhofspital Bern. In the St. Claraspital 350 left sided resections are performed per year and therefore it is the biggest contributing center. Caseload of the University Hospital Basel are 120, of the Cantonal Hospital Baselland 200, of the Cantonal Hospital Olten 85, of the Cantonal Hospital Lucerne 270, of the Spitalzentrum Biel 100, of the Cantonal Hospital Aarau 85, of the Limmattalspital Schlieren 80 and of the Lindenhofspital Bern 125 left sided resections per year.

### 2.2 Eligibility criteria

#### Inclusion criteria

All patients aged ≥ 18 years undergoing any left sided emergency or elective colorectal resections for any indication with or without primary anastomosis in one of the nine participating hospitals are eligible to be part of the study population. Patients should have given or will give a general consent for the use of their data for research purposes. As this is a quality improvement project and the modified standard according to the CB is rolled out over the entire treating institution, patients cannot opt for non-treatment according to the CB but may deny data usage and acquisition within the trial by denying general consent.

#### Exclusion criteria

No general consent given for further data use and analysis. Vulnerable patients such as minors (age < 18 years) or patients with severe dementia. Index operation is a reintervention after an earlier operation within 30d (only relevant for the starting month of the trial). Unable to provide general consent & no possibility of general consent by proxy.

## 3. Interventions

### 3.1 Intervention description

During the control period, patients are treated according to their local standard of the contributing hospitals. During this period no special interventions are planned, but baseline data will be obtained. Data according to the CRF will be collected for the pre-, intra-, and postoperative course, including all complications according to the Clavien Dindo Classification [28] for each complication to calculate the primary outcome measure (CCI) [27].

After the control period the full CB is implemented during a period of 1 month in every contributing hospital.

The CB will consist of the following items:

Preoperative optimization of the nutritional status: Perform Nutritional Risk Score (NRS), measure albumin or prealbumin preoperatively and initiate nutritional support and delay surgery by at least two weeks if clinically feasible to allow improvement of nutritional status in case the NRS is >2.Preoperative showering with an antiseptic agent on the night before or the day of admission for all patients.Antibiotic decontamination (which is optional according to institutional preference) and mechanical bowel preparation (for all).Administer preoperative antibiotic prophylaxis within 60 minutes prior to skin incision (not after and not any earlier).Hair removal in the operative field with clippers (no shaving).Peri-, intra-, and postoperative warming to maintain body temperature above 36 °C and peri-, intra- and postoperative glucose control below 9 mmol/l until patient leaves the wake-up area.Usage of a wound protection device (such as Alexis® wound protector or others).Change of gloves and instruments after anastomosis respectively the contaminated phase in patients with end colostomy formation.Anastomosis only with experienced senior surgeon present in the operating theatre for any elective and emergency procedures (senior surgeon will be defined as follows: “Schwerpunkt Träger Viszeralchirurgie” and/or “European Board of Surgical Qualification (EBSQ) Colorectal”, and/or certified operator according to Deutsche Krebs Gesellschaft (DKG) alternatively a head of department/local principal investigator can name surgeons in case of other qualification if deemed necessary).

Once these measures are completely implemented, data collection continue for another period of 6 months including prospective monitoring of compliance to CB measures. In addition, the adherence to the ERAS program will be evaluated for every single network hospital over the entire study period, to evaluate possible synergies with the ERAS program.

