### 3.7 Sample size

The sample size calculation described below is for an observational study. Simulations were used to estimate the required sample size. Specifically, we generated 1111 synthetic datasets for a range of potential sample sizes and possible reductions in CCI score due to the modified standard. We then applied the intended analysis (a linear mixed effects model with CCI as the outcome) to each of the simulated datasets. We modelled adoption of the modified standard as a fixed effect and the surgery performance of each study centre as a random effect to account for expected variation in outcomes.

The simulations are based on the following assumptions.

The modified standard will be studied in eight middle sized centres (Clarunis Site Universitätsspital Basel, Kantonsspital Aarau, Spitalzentrum Biel, Kantonsspital Baselland, Luzerner Kantonsspital, Spital Limmattal, Kantonsspital Olten and Lindenhofspital Bern) and one large centre (Clarunis Site St. Claraspital).

We assume that each middle size centre contributes n patients to each condition under study (before and after adoption of the CB) and that Clarunis Site St. Claraspital contributes 2 × n patients to each study condition.

The average CCI score pre-modified standard is 30 with a standard deviation of 12.5 [27].

The standard deviation for surgery outcomes among the centres under study is 20 (based on mortality data from the participating study centres provided by the Swiss Federal Office of Public Health) [8].

We assess the change in CCI using a linear mixed model with CCI after 30 days as the outcome variable, CB implementation as a binary factor and study centre as a random effect. The hypotheses are tested applying a one-sided Wald test for the regression coefficient estimated for the CB factor at the 2.5% Level and a target power of 90%.

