Assuming that the CB improves CCI scores by 10 points, 5 patients are needed for each study condition from each middle-sized study centre and 10 patients for each study condition from St. Claraspital. Thus, at least 10 patients should be recruited from each small study centre and 20 patients from St. Claraspital for a combined total sample of 90 patients. This sample size allows detection of an improvement on the CCI with 90% probability (power), assuming that the CB really does reduce the CCI by 10 points on average. As the study is not randomized, the models will include all potential confounders of the true association between the intervention and the outcomes in the final models. To accurately estimate this association the sample size needs to be increased by a variance inflation factor (VIF) that reflects the correlation between the intervention and the confounding factors [29]. As this is difficult to quantify, a conservative VIF of 3.3 was applied to the estimated sample size so that a total of 149 patients per arm and a total of 298 for the study. This target sample size can be realistically achieved within the study period based on current estimated caseloads in the contributing hospitals. This power calculation was performed by the statistical department of the Clinical Trial Unit (CTU) of the Department for Clinical Research of the University Basel and reviewed by an independent statistician. The CTU is a well-established and validated unit. The secondary endpoints as described above will be analysed using descriptive statistics.

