### 4.3 Statistical methods

The primary objective of the study is to be measured by the CCI 30 days post-operative compared to the CCI under standard care as the control group. The average CCI of patients treated in participating hospitals before implementation of the CB will be compared with the average CCI after implementation.

We hypothesize that the CB will be effective in reducing CCI scores 30 days post-operation as compared to standard care.

H0: The average CCI of patients treated after implementation of the CB is the same as (or higher than) the average CCI before implementation.H1: The average CCI of patients treated after implementation of the CB is lower than the average CCI before implementation.

The analysis of the primary and secondary outcomes will be made based on a one-sided Fisher`s Exact Test with the assumption of an alpha level of p < 0.05 to be considered significant. A multivariable analysis will be performed to control for the above-mentioned confounding factors concerning the primary endpoint.

For adjusted analyses, the following potential confounding factors are accounted:

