## 7. Discussion

The improvement of outcomes and reduction of complications in colorectal surgery is a highly relevant topic for patients and providers. A high rate of up to 40% of patients suffer from major complications after colorectal cancer surgery [7]. In these cases, surgical complications like anastomotic leakage will potentially lead to a worsened oncological outcome and lead to delay or even cancellation of adjuvant therapies [8]. The intended introduction of a CB to reduce postoperative complications has the potential to reduce these sometimes-life-threatening complications which is in the best interest of all patients undergoing colorectal surgery. The joint introduction of such quality improvement measures in an entire health care region like in the north western part of Switzerland allows a good generalizability of results from our study. There have been only few attempts to minimize the perioperative complication rate in colorectal surgery by introduction of standardized protocols that regulate the perioperative treatment. Studies of the past showed that standardization of these processes can lead to a reduction in postoperative complication rate, like it was shown for the introduction of the Enhanced Recovery After Surgery Protocol (ERAS) [31]. Some of the items from the colorectal bundle have also been included in the ERAS guidelines from 2018. These are preoperative nutritional care, administration of antibiotic prophylaxis 60 minutes before the procedure, antiseptic showering, bowel preparation and preventing of intraoperative hypothermia [13]. Other items such as changing gloves after the contaminated phase, presence of senior surgeon at formation of the anastomosis, antibiotic decontamination and shaving with clippers have not yet been included in the ERAS guidelines. Despite the parallels, the implementation of the ERAS Guidelines in the individual hospitals is sometimes variable. The simultaneous and binding introduction of a firmly defined treatment plan in an entire health region will help to uncover synergistic effects of the individual items and thus help to further scientifically substantiate the use of these items in the ERAS program.

There is another ongoing study of the European Society of Coloproctology investigating a quality control improvement program for right sided colorectal resections and anastomosis. To get a comprehensive picture of the treatment of these patients, we will use synergies to this EAGLE Trial [32].

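### All nine hospitals switch together, and neither the primary model nor the stated adjustment list contains calendar time, so any shift common to the hospitals is counted as bundle effect

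*Protocol article*

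**What the plan says.** The abstract sets out two consecutive blocks: "In the 6-month lasting control period the patients will be treated according to the local standard of each contributing hospital", and then "After a short implementation phase all patients will be treated according to the CB for another 6 months". Section 3.1 places the switch between them: "After the control period the full CB is implemented during a period of 1 month in every contributing hospital". Section 7 presents the common start as a strength: "The simultaneous and binding introduction of a firmly defined treatment plan in an entire health region". No hospital serves as a concurrent control.

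Section 4.3 states the primary comparison: "The average CCI of patients treated in participating hospitals before implementation of the CB will be compared with the average CCI after implementation". The model in section 3.7 has "CB implementation as a binary factor and study centre as a random effect".

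Section 3.7 adds that, because the study is not randomised, "the models will include all potential confounders of the true association between the intervention and the outcomes in the final models", and inflates the sample size by a factor of 3.3 for this. Section 4.3 then introduces the list with "For adjusted analyses, the following potential confounding factors are accounted". What follows, under the subheadings for patient and procedural factors, contains no date, month, season or trend.

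**The concern.** With one control block, one CB block and a common switch, exposure to the bundle and calendar period are the same variable. The centre random effect removes stable differences between hospitals. It does not remove a change that all hospitals share. Any such change between the two blocks, whether a trend already under way or a difference between the two halves of the year, goes into the CB coefficient.

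The article commits to adjusting for all potential confounders, yet the confounder most strongly tied to exposure in this design is not on its list. At stake is the attribution: a significant fall in CCI could be partly or wholly a time effect, and the analysis as stated could not tell the two apart. A drift in the other direction would hide a real benefit.

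**Working it through.** **Inputs from the protocol article.** Control and CB periods of 6 months each (abstract), with a 1-month implementation between them (section 3.1). SD of CCI 12.5, one-sided Wald test at 2.5%, hypothesised effect 10 points, inflation factor 3.3, 149 patients per period (section 3.7).

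**Assumptions.** Uniform accrual over months 0–6 and 7–13. Underlying falls of 0.1, 0.25 and 0.5 CCI points per month; the article gives no drift figure, so these are a range and not estimates.

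**The plan's own figure.** 45 × 3.3 = 148.5, rounded up to 149 per period and 298 in total. This last step reproduces. The base of 90 does not match its own parts (8 × 10 + 20 = 100), and section 4.3 names a different test and level from section 3.7. Both are separate matters; 149 and the section 3.7 test are used here.

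**1. Shift between periods.** The midpoints are months 3 and 10, so they are 7 months apart. Shift = 7 × monthly drift: 0.7, 1.75 or 3.5 points.

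**2. Standard error of the CB coefficient**, with centre differences removed:
- without inflation: 12.5 × √(2/149) = 1.448
- with the plan's factor: 1.448 × √3.3 = 2.631

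**3. One-sided error when the bundle has no effect.** Probability = Φ(shift/SE − 1.96).

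| Drift per month | Shift | SE 1.448 | SE 2.631 |
|---|---|---|---|
| 0 | 0 | 2.5% | 2.5% |
| 0.1 | 0.7 | Φ(0.483 − 1.96) = 7% | Φ(0.266 − 1.96) = 4.5% |
| 0.25 | 1.75 | Φ(1.208 − 1.96) = 23% | Φ(0.665 − 1.96) = 10% |
| 0.5 | 3.5 | Φ(2.417 − 1.96) = 68% | Φ(1.330 − 1.96) = 26% |

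**4. Effect of a larger sample.** The caseloads in section 2.1 sum to 1,415 a year, about 707 per half-year. As an upper bound, if all were included, SE = 12.5 × √(2/707) = 0.665, and a drift of 0.25 per month gives Φ(2.632 − 1.96) = 75%. The bias stays at 1.75 points while the standard error shrinks.

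**5. Price of a linear time term.** The variance of time between periods is 3.5² = 12.25, and within a period 6²/12 = 3. R² of CB status on time = 12.25/15.25 = 0.803, so VIF = 15.25/3 = 5.08. This alone exceeds the 3.3 that section 3.7 calls conservative. The 95% half-width at 149 per period is 1.96 × 1.448 × √5.08 = 6.4 points, against 1.96 × 1.448 = 2.8 without the term. Power for 10 points is about 87% if time is the only adjustment, and about 39% if the 5.08 multiplies the 3.3.

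**6. Season.** Each half-year is observed once, under one condition. A linear term plus a yearly harmonic has a VIF of about 15.9, with power of about 41%, or 16% with the 3.3 as well. Season cannot usefully be separated from CB with these data.

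**The case against.** Much of the opposing case is fair.

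- **Sensitivity analyses may sit elsewhere.** A reader might infer that the trial has no analysis of time trends at all. The document does not support that: it is a condensed article and the statistical analysis plan is not shown. What can be said is that the design, the primary model terms and the confounder list are fixed here, and time is in none of them.
- **Case-mix change.** A reader might infer that all case-mix change is counted as bundle effect. It is not. Section 4.3 adjusts for age, comorbidity, nutrition, indication, stage, urgency, approach, contamination and surgeon factors. Only unmeasured change remains.
- **Audit effect.** Case report form data are collected in both periods, and compliance with local standards is reviewed in the charts (sections 3.1 and 3.3). Prospective recording is therefore not peculiar to the CB period.
- **Enhanced recovery (ERAS) uptake.** Adherence is evaluated throughout (section 3.1), so data exist to examine it. The stated purpose is to look for synergies, however, and adjustment is not mentioned.
- **Size.** The introduction reports little improvement in complication rates over time. A drift of 0.25 to 0.5 per month is 3 to 6 points a year on a mean of 30, which is large against that background. Even 3.5 points is about a third of the hypothesised 10. This makes the upper end less likely. It does not exclude season or a local change, and the test is against no difference, not against 10 points.
- **Staggering the start dates** might seem the obvious remedy. It would be a redesign of a nine-hospital programme and is not asked for here. The possible extension of data collection for non-adherence (section 3.3) could move dates at some centres but is not a planned stagger.

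**Conclusion.** The point stands as a limit of the design that the stated analysis leaves unaddressed. Calendar time is aliased with CB, and the adjustment list does not contain it despite the commitment to include all potential confounders.

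Under the assumed drifts, 0.7 to 3.5 points would appear as effect. At 0.25 per month, the plan's SD and 149 per period, the nominal 2.5% error becomes about 23%, or about 10% with the 3.3 in the standard error. These figures rest on the assumed drift and uniform accrual. That a shared shift passes into the CB coefficient rests on neither. The calculation does not show that a drift exists, or that a 10-point fall would be spurious.

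**What to change.** Prespecify one sensitivity analysis on all included patients: the same adjusted mixed model, with linear month of surgery added and CB kept as a step at its start. Report it beside the primary result, with a plot of monthly mean CCI across both periods. Word the conclusion as a before-after association that cannot exclude secular or seasonal change.

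The cost is one extra model and a plot. The article does not list date of surgery as a recorded item, but a 30-day endpoint requires it. The downside is precision: a half-width of about 6.4 points before other adjustment, and wider with the full covariate list. A linear term does not remove seasonality. The analysis should therefore qualify the primary conclusion. Used as a pass/fail rule, an estimate this imprecise could discard a true effect.
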